### Study outcomes

The primary outcome will be the rate of decline in FEV_1_ and FEV_1_/FVC ratio in the intervention and control groups from baseline and follow-up. The secondary outcomes will include the change in awareness and knowledge related to COPD, quality of life of COPD patients, modification of risk factors of COPD such as active and passive smoking and change in indoor cooking behavior from baseline between the intervention and control clusters. The questionnaire-based interview and spirometry during the baseline and follow-up survey will be conducted in participants’ households using a portable diagnostic spirometer by data enumerators trained for 3 weeks.

### Trial management

To ensure data quality, a robust mechanism will be set up. Firstly, the data enumerators will receive intensive training on data collection using spirometer and questionnaire. The principal investigator will monitor data enumerators on a day-to-day basis. The data entry assistants will inspect the data manually at first and enter the data in an EpiData software file. Ten percent of the data will be double entered to qualify potential errors in data entry. There will be cross-checking the data quality on the spot and in our field office for any incomplete, inconsistent, and invalid data. Two independent pulmonologists will further review the spirometry graph for quality control. Any deviation in the data quality will require retesting in the field.

Data safety and monitoring board (DSMB) is formed secretariat at Nepal Health Research Council consisting of five members completely independent of the investigators and have no financial, scientific, or other conflicts of interest with the trial. The chairman of the board convenes DSMB meetings as conference calls as well as in person. An emergency meeting of the DSMB may be called at any time if questions of study participants’ safety arise. The change or amendments in protocol will be reported to the ethical review board of Nepal Health Research Council, DSMB, FCHVs, trial registries, and journals with relevant publications. The trial sponsor is the Department of Public Health, Aarhus University ([name]; [name]), responsible for the overall management of research planning and implementation.

### Indemnities

The trial brings very negligible risk to the study participants, so we have no compensation or insurance plan for the participants. However, 5 US dollars per home visit will be given to FCHVs for covering their transportation expenses.

### Data integrity

Data integrity will be enhanced by having data collected by trained data enumerators with a health science background and adherence to assessment protocols.

### Minimization of contamination

To minimize the contamination during the intervention, both the risk and level of contamination will regularly be monitored among both FCHVs and study participants. FCHVs will be asked not to share the study information and not to provide any support to people beyond their assigned cluster during the pre-intervention intensive training and throughout the intervention period of 1 year. Likewise, the design of the cluster will be such that intervention and control clusters will be geographically divided; hence the chance for a regular meeting of participants from two different arms of the study will be very low. In addition, all the potential ways by which the information in the intervention group influences the control participants will be followed up. If found to influence the study significantly, those factors will be adjusted during the effect estimation.

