### Randomization

The randomization approach, followed by the COBIN first trial on hypertension in Lekhnath Municipality, will be repeated in this study [30]. Out of 15 wards (clusters) in the municipality, one will be randomly excluded before randomization by lottery method. The remaining 14 clusters will be randomly assigned to the intervention and control group in 1:1 allocation ratio. The estimated sample size for the intervention study will be 1143. To include the study participants from every different sized clusters (wards), the required sample size of 1143 will be multiplied by the proportion of eligible participants in the ward. Then the intervention participants from each ward will be randomly selected. Research assistants will be blinded to the participants’ allocation status. To avoid selection bias following measures will be taken: (a) the randomization of the clusters will be done after the baseline survey, (b) clusters will not be withdrawn or added to the study, and (c) an independent epidemiologist will randomize the clusters.

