### Analysis

The primary and secondary aims of this study will be assessed using an intent-to-treat analysis. The primary outcome of the study will be the average difference in the rate of decline of FEV_1_ and FEV_1_/FVC between the intervention and control arms. We will use a mixed model ANOVA to test the statistical significance of the difference in the rate of change of primary outcomes between the intervention and control arms. Potential confounder variables statistically significantly associated with treatment assignment will be included in the multivariable analysis.

Our secondary outcomes include the change in the quality of life among people living with COPD, awareness, and knowledge on COPD, and change in magnitude of risk factors of COPD. The quality of life will be measured using the validated Nepali version of the St. George Respiratory Questionnaire [43]. The change in the quality of life will be assessed using the difference in the mean or median score at the beginning and end of the intervention accompanied by the standard deviation or interquartile range of the difference. The change in awareness and knowledge related to COPD will be assessed using the change in the proportion of people aware and knowledgeable regarding COPD. Similarly, the change in risk behaviors, including smoking and indoor cooking, will be assessed by measuring the proportion of individuals who changed those behaviors in the intervention and control clusters. The subgroup analysis will be performed based on COPD status, grade, and smoking status. Complete case analysis will be done for missing data less than 10%. In case of missing data for more than 10%, it will be addressed by the multiple imputation method. We will explain the effect of non-adherence and missing data on our results. Participants receiving three routine home visits by FCHVs during the intervention period will be considered complete adherence. We will assess two-way interaction among sex and treatment allocation, and also among smoking status and treatment allocation. STATA software (StataCorp, College Station, TX, USA) will be used for the data analysis of the study.

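### The contamination rule lets the effect estimate be adjusted for something that happens after randomisation, and the stated ward allocation does not support the claim that the arms are geographically divided

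*Protocol article*

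**What the plan says.** The section on minimization of contamination in the protocol article contains three relevant elements.

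- **Monitoring.** "To minimize the contamination during the intervention, both the risk and level of contamination will regularly be monitored among both FCHVs and study participants". It adds that "all the potential ways by which the information in the intervention group influences the control participants will be followed up".
- **Adjustment.** "If found to influence the study significantly, those factors will be adjusted during the effect estimation".
- **Reassurance.** "the design of the cluster will be such that intervention and control clusters will be geographically divided", from which the article concludes that "the chance for a regular meeting of participants from two different arms of the study will be very low".

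The Analysis section states: "The primary and secondary aims of this study will be assessed using an intent-to-treat analysis". It makes no exception for contamination.

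The Randomization section fixes the timing, "the randomization of the clusters will be done after the baseline survey", and the method, "The remaining 14 clusters will be randomly assigned to the intervention and control group in 1:1 allocation ratio". The Clusters section adds that one of the 15 wards is dropped by lottery before allocation.

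**The concern.** Contact of control participants with the intervention's messages is a consequence of which wards were allocated to the intervention. It is also, in substance, a partial dose of the treatment. An arm comparison that conditions on it no longer compares the groups that randomisation formed, so the result cannot be described as intent-to-treat.

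The trigger makes this worse. The article does not say what counts as a significant influence, who decides, or on what data. In an open-label trial, whether the headline estimate is adjusted could then depend on what the data show.

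The geographic statement matters for interpretation. A reader who accepts that contact between arms is very unlikely will discount dilution as an explanation for a small or null effect, and the planned contrast is only 19 ml of FEV1.

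**Working it through.** **1. Timing**

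| Step | Section | Order |
|---|---|---|
| Baseline survey | Randomization | first |
| Wards randomised | Randomization | after the baseline survey |
| FCHV training and 12 months of home visits, in intervention wards | Study intervention | after randomisation |
| Contamination monitored | Minimization of contamination | during the intervention |
| Adjustment if judged significant | Minimization of contamination | at effect estimation |

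The factors to be adjusted for are ways in which intervention-arm information reaches controls. They can exist only once there is an intervention arm, so they come after randomisation and depend on it.

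**2. What adjustment would estimate**

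The document gives no contamination rate, so this is an illustration. Let the planned contrast be d = 19 ml (Sample size calculation). Let a share c of controls be contaminated, and assume each receives the full effect. Let s be the amount by which contaminated controls would have differed from the average control anyway.

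- *Intent-to-treat:* d × (1 − c). At an assumed c of 10%, 19 × 0.90 = 17.1 ml. At 20%, 19 × 0.80 = 15.2 ml. This is dilution, not bias from adjusting.
- *Exposure recorded in both arms, all intervention participants exposed (assumed):* the arm coefficient compares intervention participants with contaminated controls, so d − (d + s) = −s. With s = 0 this is 0 ml.
- *Exposure flagged in controls only:* the arm coefficient compares all intervention participants with uncontaminated controls. These differ from the average control by −cs/(1 − c), so the target is d + cs/(1 − c). With s = 0 this is 19 ml.

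The same data can therefore give 0 or 19 ml depending on coding alone, and s is unknown because it was not fixed by randomisation. The article does not state the coding.

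**3. Geography**

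Inputs: 15 wards of one former municipality (Study Settings), one dropped by lottery (Clusters), 14 allocated at random 1:1 (Randomization). No buffer, matching or spatial restriction is stated.

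- Once one ward is placed, 7 of the other 13 are in the opposite arm. P(two given wards in opposite arms) = 7/13 = 53.8%, on any map. The expected share of borders between trial wards that separate the arms is therefore also 53.8%.
- For a ward with k neighbouring trial wards, P(at least one in the other arm) = 1 − C(6,k)/C(13,k):
  - k = 2: 1 − 15/78 = 81%
  - k = 3: 1 − 20/286 = 93%
  - k = 4: 1 − 15/715 = 98%
- No ward map is shown, so two layouts were assumed and every combination enumerated: 15 exclusions × C(14,7) = 15 × 3,432 = 51,480.

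| Assumed layout | Combinations with no shared border between arms | Control wards touching an intervention ward, on average |
|---|---|---|
| 3 × 5 grid | 0 | 88% |
| Single line | 0.004% | 73% |

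**The case against.** Several points on the other side have force.

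- **The adjustment is conditional.** A reader might infer that the effect will be adjusted in any event. The text does not say so: it applies only if contamination is judged significant. The word may also mean material rather than statistically significant, so selection on the result is a risk, not a stated intention.
- **It might be meant as a secondary estimate.** The sentence does not name the primary analysis, and a contamination-adjusted estimate could sit beside the intent-to-treat one. That would be acceptable, but the sentence speaks of the effect estimation without limitation, and the Analysis section provides no such second estimate. This is a stated rule that needs limiting, not detail left to an analysis plan.
- **The factors might be pathways, not individual exposure.** A fixed ward characteristic known before allocation would be a legitimate covariate if specified in advance. The article instead describes influences found during follow-up.
- **Geography is one safeguard among several.** FCHVs are told not to share study information or support people outside their cluster, and contamination is monitored. This stands, and it matters because FCHV home visits deliver the intervention.
- **The separation claim might be right.** A reader might infer from the arithmetic that the claim is false or that separation is impossible. The document does not support that. There is no map, the first COBIN trial's randomisation approach, which is to be repeated, is not shown, and a shared border is not the same as regular contact. The claim could also mean only that each ward is a distinct area, but that reading would not support the conclusion drawn about contact between arms.

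**Conclusion.** The point holds in two parts.

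**Adjustment (the main part).** As written, the article permits a data-triggered adjustment of the effect estimate for a post-randomisation consequence of allocation. That conflicts with its intent-to-treat commitment. The size of the resulting bias cannot be derived from the document. The 0 and 19 ml results only show that the target depends on an unstated coding, assuming contaminated controls receive the full effect and are otherwise typical. The 17.1 to 15.2 ml range should not be read as bias from adjusting: it is intent-to-treat dilution under an assumed 10 to 20% contamination, and it would remain after the fix.

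**Geography (the smaller part).** The described allocation contains nothing that divides the arms. The 7/13 figure needs no map, only unrestricted random allocation. The grid and line results rest on assumed layouts. The supportable conclusion is that very low cross-arm contact does not follow from the design as described, not that contact is known to be high.

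**What to change.** Replace the adjustment sentence with:

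> The primary estimate is intent-to-treat and is not adjusted for contamination or any other post-randomisation variable. Exposure reported in control wards is tabulated. Any contamination-adjusted estimate is supplementary only.

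If a supplementary estimate is wanted, define the exposure variable and method before outcomes are compared by arm. An analysis using ward assignment as an instrument is one option, but with 14 wards it is not essential.

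Replace the statement that the arms are geographically divided with the number of ward borders that separate an intervention from a control ward after allocation. State that contamination would dilute the intent-to-treat effect.

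The cost is wording plus one descriptive table. The Trial status section reports recruitment complete in September 2019, so the borders should be countable from the actual allocation. One limit remains: the follow-up question described under Intervention fidelity covers visits and counselling by FCHVs, so it may miss information passed informally between residents. The table should say so, or a question should be added if data collection still allows.

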### Intervention fidelity

The fidelity of the study will be guaranteed, starting from the pre-intervention training to FCHVs. They will be explained about the importance of enduring with all the constituents of intervention in the experimental arm. Similarly, FCHVs in the intervention arm will receive a register to record and report all activities. They will report to the project team every four months, and the field coordinator will meet regularly to monitor the FCHVs’ activities. Supervision checklists will be used to track and update the knowledge and skill levels of FCHVs. At the follow-up survey, the data enumerators will ask the participants about the visits and counseling made by FCHVs.

### Interim analyses and stopping rules

The study does not have an interim analysis plan, as we do not expect a situation that would lead us to study termination. However, the study will be temporarily stopped to assess the implications on the study design if an extreme situation occurs, such as a natural disaster, a conflict, or duplication of similar interventions in our control area.

### Dissemination of results

The study results will be shared through workshops, local and international conferences, seminars, and events organized with local stakeholders. We plan to publish the results of this trial as a peer-reviewed publication.

## Discussion

WHO data show that over 90% of deaths from COPD occur in low- and middle-income countries [2]. Most of this is attributable to air pollution (indoor and outdoor) and tobacco smoke. These are the very countries that face significant challenges in spreading awareness of chronic lung diseases and their risk factors among the public and decision-makers. Additionally, access to clinically efficient and cost-effective interventions and the provision of diagnosis and treatment services are inadequate. Therefore, there is an urgent need to develop suitable solutions to the local context and, at the same time, feasible in terms of cost and clinical effectiveness. In a resource-constrained setting like Nepal, with very limited health service provision on chronic disease prevention and management, especially on chronic respiratory diseases like COPD. The approach for task-sharing to community health workers could be one of the best options. Mobilizing community health workers, i.e., FCHVs in Nepal, have shown promising results in other public health issues and chronic disease prevention and management like hypertension and diabetes [31, 32]. This study capitalizes on the experience, knowledge, and skills of FCHVs in the prevention and management of COPD. This approach is expected to serve as a potential way to address the neglected issue of COPD in Nepal. Its success will also potentially serve as a guide to national scale-up and similar efforts in low- and middle-income countries elsewhere.

## Trial status

The trial has been closed to participant recruitment, but the trial is ongoing. The trial recruitment began on 1 May 2019 and was completed on 28 September 2019. At the end of March 2021, we will complete the endpoint assessment of all the participants. At the end of April 2021, we will complete the outcome assessment of all the participants. The schedule of enrollment, interventions, and assessments is presented in Fig. 2. The trial protocol has been submitted for publication after the end of recruitment due to a delay in finalizing the manuscript affected by the author’s travel plan for fieldwork considering the tight timeline of the Ph.D. study of the principal investigator. However, the study protocol was registered to clinicaltrials.gov before starting the baseline survey.

**Fig. 2 Fig2:**
[figure not shown]
Schedule of enrolment, interventions, and assessments (SPIRIT figure)

The protocol version number and date: V1, 16 April 2020.

## Data Availability

Final trial data are available upon reasonable request to the principal investigator of the study.

## Abbreviations

ATS: American Thoracic Society
CHWs: Community Health Workers
COPD: Chronic obstructive pulmonary diseases
COBIN: Community-based Management of Non-communicable Diseases in Nepal
cRCT: Cluster randomized controlled trial
DSMB: Data safety and monitoring board
ERS: European Respiratory Society
FCHVs: Female Community Health Volunteers
FEV_1_: Forced expiratory volume in 1 s
FVC: Forced vital capacity
GOLD: Global Initiative for Chronic Obstructive Lung Disease
LMICs: Low- and middle-income countries
NCDs: Non-communicable diseases
SPIRIT: Standard Protocol Items: Recommendations for Interventional Trials
WHO: World Health Organization
